## Abstract

**Background:** Prostate cancer is the most common non-cutaneous malignancy in men. Today most patients may expect to live years following the diagnosis and may thus experience significant morbidity due to disease progression and treatment toxicity. In order to address some of these problems exercise has been suggested and previously studies have shown improvements of disease specific quality of life and a reduction in treatment-related toxicity. Cohort studies with long term follow up have suggested that physical activity is associated with improved survival in prostate cancer patients. Previously one randomised controlled trial has examined the efficacy of football in prostate cancer patients undergoing androgen deprivation therapy to usual care and reported positive effects on lean body mass and bone markers. Against this background, we wish to examine the effectiveness of community-based football for men diagnosed with prostate cancer.

**Methods:** Using a randomised controlled parallel group, multicenter, superiority trial design, two hundred prostate cancer patients will be recruited and randomised (1:1) to either community-based football one hour twice weekly or to a control group. The intervention period will be six months. The primary outcome is quality of life assessed after 12 weeks based on the change from baseline in the Functional Assessment of Cancer Therapy–Prostate questionnaire. Secondary outcomes are change from baseline to six months in quality of life, lean body mass, fat mass, whole body and regional bone markers, as well as physical activity and functional capacity at 12 weeks and six months. Safety outcome variables will be falls resulting in seeking medical assessment and fractures during the six-month period.

**Discussion:** Football is viewed as a case for non-professional, supervised community-based team sport for promoting long-term physical activity in men diagnosed with prostate cancer. This randomised trial will provide data on effectiveness and safety for men with prostate cancer when football training is delivered in local football clubs.

**Trial registration:** Clinicaltrials.gov identifier: NCT02430792

**Keywords:** Prostate cancer, Soccer, Exercise, Physical activity, Quality of life

\* Correspondence: [contact]

University Hospitals Centre for Health Research (UCSF), Rigshospitalet, University of Copenhagen, Copenhagen, Denmark

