## Objective

The primary objective of the FC Prostate Community Trial (FCPC) trial is to determine whether community-based football is superior to usual care for improving cancer-specific QoL after 12 weeks of participation.

The secondary objectives are to determine whether community-based football is superior to usual care for improving PCa-specific QoL, lean body mass, fat mass, bone mineral density and bone mineral content after six months and functional well-being and physical activity after 12 weeks and after six months. The safety of the intervention will also be evaluated based on falls resulting in seeking medical assessment and fractures after six months.

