### The football intervention

Participants allocated to the intervention group will be offered one hour of recreational football twice weekly. The football training sessions consist of a 20-min warm-up based on the FIFA11+ concept, though modified to suit older players [27]. Next, participants will spend 20 min practising dribbling, passing and shooting. The training sessions will then end with 20 min of 5–7-a-side football. Two coaches recruited from the local football club will be in charge of all training sessions. The coaches are expected to have experience as either a player or coach but no other formal qualifications are required. The coaches will be required to have passed a first-aid course and to complete a 10-h course involving lectures on PCa treatment, patient experiences of PCa and a manual describing the content of the training, including the FIFA 11+ concept intended to prevent injuries. Participants will be told to avoid hard tackles and other actions that carry a risk of injury. In the event of injuries participants will remain in their allocated group and will be encouraged to participate in football practice again after recovery. Adherence to the intervention will be recorded by the coaches. Participants

allocated to football training will be able to track their individual adherence and compare it to an average adherence rate of participants in the football group. A logical model, presented in Table 2, summarises the key inputs, activities and intended outputs of the intervention, while Fig. 2 presents the activities and Fig. 3 shows the assumed causal pathways for the effect of the intervention on the individual.

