| Fat mass                        | Whole-body fat mass                                                 | Change from baseline           | Mean                  | 6 month             |
| Whole body bone strength        | Whole-body bone mineral content                                     | Change from baseline           | Mean percent          | 6 month             |
|                                 | Whole-body bone mineral density                                     | Change from baseline           | Mean percent          | 6 month             |
| Self-reported physical activity | International Physical Activity Questionnaire                       | Change from baseline           | Mean                  | 12 week and 6 month |
| Functional well-being           | Subscale from Functional Assessment of Cancer Therapy-Questionnaire | Change from baseline           | Mean                  | 12 week and 6 month |
| Regional bone strength          | Lumbar spine bone mineral density                                   | Change from baseline           | Mean percent          | 6 month             |
|                                 | Femoral neck bone mineral density                                   | Change from baseline           | Mean percent          | 6 month             |
|                                 | Total hip bone mineral density                                      | Change from baseline           | Mean percent          | 6 month             |
| Safety                          | Participants with any fracture                                      | Number in each group           | Proportion            | 6 month             |
|                                 | Participants with falls that resulted in seeking medical assessment | Number in each group           | Proportion            | 6 month             |
| Exploratory outcomes            |                                                                     |                                |                       |                     |
| Dyadic adjustment               | DAS-7                                                               | Change from baseline           | Median                | 12 week and 6 month |

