### Secondary outcomes including safety outcomes

Changes from baseline to six months for LBM, BMD, BMC and total body fat mass will be analysed in the same manner as the primary outcome.

QoL, functional well-being and physical activity (based on metabolic equivalent of task values derived from IPAQ) measured at baseline, 12 weeks and six months will be analysed using a mixed model for repeated

measurements. Changes from baseline to 12 weeks or six months will be treated as the response. The model will include fixed effects of factors: group, ADT, sampling time and their interactions, and the analysis will be adjusted for age and baseline value. The correlation between measurements on the same participant will be modelled using a random effect of participant.

Safety outcomes will be listed for each group and the number of falls that resulted in seeking medical assessment and fractures will be compared across groups using Fisher's exact test.

Subgroup analyses will be reported for the patients treated with ADT, which means that results will be given for both the overall treatment effect and for the subgroup obtained by stratifying according to ADT. To verify the credibility of our subgroup analyses, we will apply the criteria proposed by Sun and colleagues [33], i.e. the subgroup variable is a baseline characteristic, a stratification factor, specified a priori and includes only a small number of analyses.

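### The safety test should be worded in participants, as in Table 3, and the safety outcomes leave out medically attended football injuries that are neither fractures nor due to falls

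*Protocol*

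**What the plan says.** **The test.** Under the heading on secondary outcomes including safety outcomes, the Protocol states that "the number of falls that resulted in seeking medical assessment and fractures will be compared across groups using" Fisher's exact test. It also says that safety outcomes will be listed by group.

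**The outcome definition.** Table 3 gives two safety variables: "Participants with any fracture" and "Participants with falls that resulted in seeking medical assessment". For both, the metric is the number in each group, the aggregation is a proportion, and the time point is six months.

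**The scope.** The Objective section says: "The safety of the intervention will also be evaluated based on falls resulting in seeking medical assessment and fractures after six months". The Abstract names the same two: "Safety outcome variables will be falls resulting in seeking medical assessment and fractures during the six-month period". No other safety outcome appears.

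**Injury.** The section on the football intervention describes a warm-up concept meant to prevent injuries and tells players to avoid hard tackles and other risky actions. It also sets out what happens to injured men: "In the event of injuries participants will remain in their allocated group".

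**The promise.** The Abstract says: "This randomised trial will provide data on effectiveness and safety for men with prostate cancer".

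**The concern.** There are two separate matters.

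1. *Unit of analysis.* A man can fall more than once, so a number of falls is not a number of men. Fisher's exact test works on independent binary units. Taken literally, the methods sentence gives the test a quantity that does not fit a two-by-two table of participants, and it disagrees with Table 3. If events were entered, a few repeat fallers could drive the p-value for harm.

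2. *Scope.* The Protocol foresees injury as a consequence of the intervention, but its safety outcomes catch an injury only by way of a fracture or a fall that led to medical assessment. A torn muscle, a tendon or ligament injury, or a collision without a fall falls outside both, even if it needed medical care. An excess of such injuries in the football arm would not show in the between-group safety comparison.

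**Working it through.** **Inputs.** The planned size is 100 per arm (sample size section). It reproduces from a difference of 6, an SD of 15, two-sided 5 % and 80 % power: n = 2 × (1.960 + 0.842)² × 15² / 6² = 98.1, so 99 per arm against the stated 100. It serves below only as the denominator. The Protocol gives no fall, fracture or injury rates, so every safety count below is an assumption.

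**Step 1: what the unit does to the p-value.** Suppose 4 men in one arm have 10 falls between them, and 2 men in the other arm have 2.

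- By participants, 4/100 versus 2/100. With 6 fallers in total, the only split more probable than the observed one is 3 versus 3. Its probability is C(100,3)² / C(200,6) = 0.317. Two-sided p = 1 − 0.317 = 0.683.
- By falls entered as if they were men, 10/100 versus 2/100. The tail probabilities for 10, 11 and 12 of 12 are 0.01403, 0.00232 and 0.00017, which sum to 0.01652. Two-sided p = 2 × 0.01652 = 0.033.

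A second assumed case goes the same way. With 5 versus 1 men, p = 0.21. If those 5 men had 9 falls and these were entered as 9/100 versus 1/100, p = 0.018.

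**Step 2: type I error.** The null was simulated with 20,000 runs per setting, 100 men per arm and a nominal level of 5 %. Falls per man were Poisson, or negative binomial with variance μ + μ²/k, where a smaller k means stronger clustering within men. Rejection rates when falls are entered as if they were men:

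| Assumed mean falls per man (μ) | Poisson | k = 0.5 | k = 0.2 | k = 0.1 |
|---|---|---|---|---|
| 0.05 | 2.4 % | 3.2 % | 4.4 % | 6.0 % |
| 0.10 | 3.7 % | 6.1 % | 8.8 % | 13.7 % |
| 0.20 | 5.7 % | 10.4 % | 17.6 % | 26.7 % |

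Counting participants instead gives 1.7 % to 3.3 % across all settings. Inflation from counting falls therefore needs clustering and a fairly high rate together. Without clustering the test stays near its nominal level.

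**Step 3: which injuries the safety outcomes catch.** No arithmetic applies here, so the kinds of injury are set against Table 3.

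| Injury in a participant | Counted in Table 3? |
|---|---|
| Fracture, from any cause | Yes |
| Injury from a fall that led to medical assessment | Yes, through the fall |
| Muscle, tendon, ligament or collision injury without fall or fracture, medically assessed | No |

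The planned listing by group and the publication table by group and type do not close this gap, because both present safety outcomes as already defined.

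**The case against.** The strongest reply on the unit is that the Protocol settles it. The Outcomes section names Table 3 as the place where every outcome's variable, metric and aggregation are specified, and the table says participants and proportion. The Abstract and the Objective use the same short form as the methods sentence. Fisher's test itself implies a participants-with/without table, and no rate or count model is mentioned. This stands. A reader might infer that the planned test is invalid, or that falls will be entered as if they were men, and the documents do not support that. The 0.03 in the illustration needs 2.5 medically assessed falls per faller in one arm, and the 26.7 % needs strong clustering at the highest assumed rate. Nothing in the Protocol supports either. What remains is that two current statements differ and should agree.

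On scope, the reply is that the Protocol names the same two outcomes throughout, that fractures and falls suit a trial with bone outcomes and an osteoporosis exclusion, and that foreseeing injury does not contradict a narrow safety endpoint. It is true that there is no contradiction. The narrow endpoint still leaves out part of the harm that the intervention section anticipates, while the Abstract promises data on safety.

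Two further readings go too far. One is that cardiac or other acute events are a gap of the same kind; the intervention section anticipates injuries, not those. The other is that injuries will go unrecorded. The Data collection section names no injury item, but it names none for falls or fractures either, so its silence proves nothing about recording. The supportable statement is that other injuries are not defined as a safety outcome.

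Finally, self-reported injury in an unblinded trial, where one arm meets coaches twice a week, may be ascertained differently by arm. That is a real cost of the remedy.

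**Conclusion.** The concern holds in two parts of unequal weight.

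- *Unit:* a minor inconsistency of wording. Table 3 is the better guide and fits the test. The p-value shifts (0.68 to 0.03, and 0.21 to 0.018) and the simulated error rates are illustrations under assumed counts and rates, not predictions for this trial.
- *Scope:* a real gap in outcome definition. Followed exactly, the plan leaves medically attended injuries without a fall or fracture out of the randomised safety comparison. Its size cannot be stated, because no injury rate is given. Which harms count as outcomes in both arms belongs in the protocol; an analysis plan cannot recover data that were not collected.

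The primary outcome, its analysis and the sample size are unaffected.

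**What to change.** 1. In the section on secondary and safety outcomes, state that Fisher's exact test compares the number of participants with at least one medically assessed fall and, separately, the number with any fracture, as in Table 3. List event counts descriptively by group. This costs a few words.
2. Add participants with any injury leading to medical assessment, over six months, as a safety outcome in Table 3, the Objective and the Abstract. Ascertain it identically in both arms, for example by one item in the 12-week and six-month web questionnaires. The Protocol does not say where falls and fractures are collected, so state the source for all three outcomes together.

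The second change needs an amendment through the route in the Ethics section. It adds a slight burden for participants, and its data would be self-reported and open-label. The medical-assessment threshold limits that weakness but does not remove it.

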### Sample size and power considerations

The sample size calculation is based on the detection of a minimal clinical important difference between groups on six points on the FACT-P questionnaire [28] at 12 weeks with a standard deviation of 15 FACT\_P points. A two-sided significance level of 5 % and power of 80 % were chosen; The standard deviation is based on a previous exercise trial [30] but increased slightly as FCPC participants will be more heterogeneous than the participants in that trial. Consequently, 100 participants will be needed in each group, i.e. 200 participants in total, in order to detect a statistically significant difference between groups. No interim analysis will be performed. However, if the

anticipated sample size has not been enrolled by 1 May 2017, recruitment will end and final analyses will be performed with the number of patients recruited at that point.

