### Primary outcome

The continuous FACT-P outcome score will be calculated using the official scoring guideline. As described in the scoring guideline missing items will be prorated by multiplying the sum of the subscale with the number of the items in the subscale, then divided by the number of items answered. This will be done if more than 50 % of the items are answered in the subscales and 80 % are answered in the total questionnaire. The change score of the total FACT-P at 12 weeks will be calculated by subtracting the total 12-week score from the respective trial participant's baseline score. Analysis of covariance will be used [32], group and ADT status will be set as factors, the response will be change in FACT-P and covariates will be age and baseline score. The results will be presented as least squares means (LSMEANS) differences between the two groups with 95 % confidence intervals and *p*-values.

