#### **Outline of figures and tables**

The first figure in the main publication will be a CONSORT diagram and the second figure will illustrate changes in the primary and secondary outcomes, with the exception of safety outcomes, at 12 weeks and six months, according to treatment group.

A third figure will display mean curves for the primary outcome for participants in different groups according to the pattern of missing data. In particular, mean curves will be shown separately for completers and participants with missing data at one or more assessment times. The figure will be used to guide the type of sensitivity analyses performed to adjust results for a potentially deviating pattern for patients with incomplete observations.

The main publication will also include three tables, one delineating the characteristics of trial subjects, one showing changes in primary and secondary outcomes at 12 weeks and at six months, and one presenting safety outcomes according to group and type.

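### The only between-group inference fixed for falls and fractures is a low-powered Fisher's exact test; a risk difference with a 95 % confidence interval would serve the safety objective better at almost no cost

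*Protocol*

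**What the plan says.** The Objective section makes safety one of the trial's aims: "The safety of the intervention will also be evaluated based on falls resulting in seeking medical assessment and fractures after six months". The Abstract promises the same: "This randomised trial will provide data on effectiveness and safety for men with prostate cancer when football training is delivered in local football clubs".

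Table 3 sets the unit of analysis. Fractures are counted as "Participants with any fracture", falls are counted in the same way by participant, and both are summarised at six months as the number and proportion in each group.

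The analysis is in the section on secondary outcomes including safety outcomes. It begins "Safety outcomes will be listed for each group" and goes on to say that falls leading to medical assessment and "fractures will be compared across groups using Fisher's exact test". The outline of figures and tables adds a table to the main publication, "one presenting safety outcomes according to group and type".

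For the primary outcome the protocol specifies more: "The results will be presented as least squares means (LSMEANS) differences between the two groups with 95 % confidence intervals", together with p-values. The DXA outcomes are to be analysed in the same manner. The sample size, "Consequently, 100 participants will be needed in each group, i.e. 200 participants in total", rests on FACT-P alone.

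**The concern.** A test of difference asks whether the data rule out equal risks. A safety objective needs to know how large an excess the data leave open. With few events in a trial of 200 men these questions can have very different answers: a p-value well above 0.05 can go with an interval that still contains a substantial excess of harm.

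The protocol fixes an estimate with an interval for benefit, but for harm it fixes only a test beside the raw counts. The Discussion says the trial is meant to inform decisions on using football in community clubs. Readers with that decision to make need the size of harm still compatible with the data, and the p-value does not give it.

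**Working it through.** **Inputs from the protocol.** 100 men per group, 1:1 allocation, two-sided 5 % level, FACT-P difference 6, SD 15, 80 % power. The safety outcomes are participants with at least one event by six months.

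**Inputs assumed.** The protocol gives no event rates, so I take control six-month risks from 1 % to 20 %. All men are taken as evaluable and the level is unadjusted for multiplicity. Loss to follow-up or an adjustment would lower the power.

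**Step 1: the plan's own figure.** n per group = 2(1.960 + 0.842)² × 15² / 6² = 2 × 7.849 × 6.25 = 98.1, so 99. With a t distribution, 100 per group gives power 0.804. The stated 100 per group reproduces. It has no bearing on falls or fractures, for which no power is claimed.

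**Step 2: power of the planned safety test.** Let X be the events among 100 football men and Y those among 100 control men, independent binomials with risks p₁ and p₀. Power is the sum of P(X = x) × P(Y = y) over all pairs (x, y) whose two-sided Fisher p is at most 0.05. For a true doubling:

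| Assumed control risk | Football risk | Power | Missed |
|---|---|---|---|
| 1 % | 2 % | 0.6 % | 99.4 % |
| 2 % | 4 % | 4.4 % | 95.6 % |
| 3 % | 6 % | 9.1 % | 90.9 % |
| 5 % | 10 % | 19.0 % | 81.0 % |
| 10 % | 20 % | 44.4 % | 55.6 % |
| 15 % | 30 % | 66.9 % | 33.1 % |
| 20 % | 40 % | 84.4 % | 15.6 % |

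For a true tripling, power is 3.4 %, 17.1 %, 32.6 % and 58.6 % from control risks of 1 %, 2 %, 3 % and 5 %. If 85 men per group were evaluable, a doubling would be missed 99.7 % of the time from 1 % and 62.9 % from 10 %.

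**Step 3: what the test shows and what an interval shows.** Fisher's p is set beside the Newcombe 95 % interval for the risk difference, football minus control. That interval is built from the Wilson limits (l, u) of each proportion: with d = p₁ − p₀, lower limit d − √[(p₁ − l₁)² + (u₀ − p₀)²] and upper limit d + √[(u₁ − p₁)² + (p₀ − l₀)²], using observed proportions.

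For 4/100 against 2/100, the Wilson limits are 1.57 % to 9.84 % and 0.55 % to 7.00 %, and d is 2 points.
- Lower: 2 − √[(4 − 1.57)² + (7.00 − 2)²] = 2 − 5.56 = −3.6 points.
- Upper: 2 + √[(9.84 − 4)² + (2 − 0.55)²] = 2 + 6.01 = +8.0 points.

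| Events, football vs control (of 100 each) | Fisher p | 95 % interval, points |
|---|---|---|
| 2 vs 1 | 1.00 | −3.7 to +6.1 |
| 4 vs 2 | 0.68 | −3.6 to +8.0 |
| 10 vs 5 | 0.28 | −2.6 to +13.0 |
| 5 vs 0 | 0.059 | +0.3 to +11.2 |
| 7 vs 1 | 0.065 | +0.3 to +12.8 |

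In the first three rows an unremarkable p-value goes with an interval that leaves a sizeable excess open. In the last two, the Newcombe interval lies just above zero although Fisher's conservative test stays above 0.05. With one event in the control group, the football group needs at least eight before the test reaches 0.05.

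**The case against.** Several counter-arguments have force.

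- **Safety is not judged by a p-value alone.** The listings, the numbers and proportions in Table 3 and the safety table will all be available, and any reader can compute a risk difference and interval from them. This stands. Fisher's test is the only stated between-group inference, not the only safety information.
- **No rule equates non-significance with safety.** A reader might infer that a result above 0.05 is meant to be reported as safe. The documents do not support that: safety is to be evaluated and data provided, with no hypothesis of equivalence or non-inferiority. The masked interpretation described under Blinding also gives some protection against a motivated reading.
- **The miss rates rest on assumed event rates.** This also stands. The 56 % to 99 % range belongs to control risks of 1 % to 10 %, and the test does much better at 15 % or 20 %. It cannot be said that almost any plausible excess would be missed.
- **Low power for rare harms is normal in a trial sized on efficacy.** True, and it is no fault in the sample size. It is the reason to report an interval.
- **An interval is detail for a statistical analysis plan.** That plan is not at hand and may contain one, so absence from the protocol is not an error. But the protocol has already chosen a method for this comparison, and a more informative one is available. Fisher's test itself suits sparse participant counts.

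**Conclusion.** The point holds as a cheap improvement. With 100 men per group, the only between-group inference the protocol fixes for its safety outcomes misses a true doubling about 56 % to 99 % of the time if control risks lie between 1 % and 10 %, about 33 % at 15 % and 16 % at 20 %. All these rates are assumptions, because the document states none; the calculation also assumes full follow-up and an unadjusted two-sided 5 % level. Across the lower range, a non-significant test could not on its own support a statement that football is safe. The protocol makes no such statement, but neither does it specify an estimate that would guard against one. It does not follow that the plan is wrong, that the trial needs more men, or that its authors would misread the result.

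**What to change.** In the section on secondary outcomes including safety outcomes, add wording to this effect:

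*For participants with any fracture, and for participants with a fall leading to medical assessment, the risk difference (football minus control) at six months will be reported with a 95 % confidence interval (for example Newcombe). Fisher's exact p-value will be given as descriptive. The safety statement will be based on the interval, and a non-significant test will not be taken as evidence of no excess harm.*

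Naming participants as the unit also brings the text, which speaks of the number of falls, into line with Table 3. Fisher's test suits the participant count. Because the interval and the test can disagree near the boundary (5 vs 0 and 7 vs 1 above), it helps to settle beforehand that the interval carries the interpretation. No margin needs to be prescribed.

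The cost is a few sentences and one extra interval per outcome, from data already collected and with no additional participants. The drawback is that the intervals will be wide and the safety statement correspondingly more cautious.
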